## Methods

### Overview

All procedures in this study have been approved by the institutional review board (IRB) of the University of California, Los Angeles, which serves as the single IRB of Record for researchers at collaborating institutions. This is 1 of 3 studies in a National Institute of Child Health and Human Development (NICHD)-funded U19 Cooperative Agreement for the Adolescent (HIV Medicine) Trials Network (ATN) as well as a Management Core and Analytic Core [17,44-47]. This study began recruitment in May 2017. From June 2018 to December 2018, the protocol underwent a process of review and revision in collaboration with NICHD project scientists, the study’s scientific monitoring committee, and an external statistical expert, to meet budget constraints and align more closely with ATN scientific priorities. The major changes were (1) to reduce STI testing frequency from every 4 months routinely to only at baseline, 12, and 24 months and rectal testing only (unless requested by youth or indicated by symptoms); (2) stopping follow-up and intervention at 12 months with youth who are not MSM or transgender; and (3) changing randomization allocations for person-mediated intervention arms to have statistical power for MSM and transgender participants with 70% retention rates.

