### Design

Figure 1 shows the study design overview. The randomized controlled factorial design assesses efficacy of 3 intervention strategies (arms 1-3) and their combination (arm 4). The person-mediated interventions in arms 2 to 4 have a sample size of 270 per arm with 220 MSM and transgender youth, whereas the larger sample of 690 in the automated intervention only (arm 1) is because of the broader U19 Cooperative Agreement’s goal to identify youth acquiring HIV infection during follow-up to refer to a sister protocol on acute HIV infection [45], and earlier expectations to recruit youth that could be referred to other ATN protocols. Participants are followed longitudinally over 24 months (12 months for youth who are not MSM or transgender) and assessed at 4-month intervals by interviewers. Participants also complete a brief 7-question survey every week by text message (or email when nonresponsive to text messages). The overviews of assessments are provided below and described in detail in linked publications for the U19 [17,44-47].

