###### Aim 1: To Assess the Independent and Synergistic Effects of the Interventions on the HIV Prevention Continuum Outcomes

Multilevel models (MLMs) will be used to test the impact of the intervention on HIV prevention continuum indicators and secondary outcomes over time shown in Textbox 1 in the Background section. MLMs are needed to account for the hierarchical nature of the data and model correlations between repeated observations to properly estimate standard errors on regression coefficients. MLMs are flexible in handling discrete outcomes, such as binary HIV-prevention-continuum indicators (yes/no) and continuous outcomes, such as mental health measures. The MLM analyses will contain main effects for peer support (PEER_i_) and coaching (COACH_i_), as well as a 2-way interaction between peer support and coaching compared with AMM alone. This model parameterization will allow us to test independent effects of peer support and coaching and their synergistic effects on outcomes. MLMs contain interactions between TIME and intervention effects to test for changes in outcome levels between intervention arms over time (our primary goal). Equation 1 shows a random intercept (RI) model that will provide a starting point in the modeling process. Let Y_it_ be an outcome for person i at time point t and let η_it_ be a link function for outcome Y_it_, such as a logit link for binary prevention-continuum indicators. An MLM with a random effect λ_i_ to capture correlations between repeated observations for each person is expressed as:

η_it_ = β_0_ + β_1_ PEER_i_ + β_2_ COACH_i_ + β_3_ TIME_it_ + β_4_(PEER_i_ x TIME_it_) + β_5_(COACH_i_ x TIME_it_) + β_6_(PEER_i_ x COACH_i_ x TIME_it_) + λ_i_. (1)

We will also fit MLM with other covariance structures that we have used in previous HIV intervention studies, including RI and slope (RIAS) and autoregressive covariance structures. The covariance structure with the best fit statistics will be selected. Covariates for demographics and other background characteristics may need to be added to Equation (1) if imbalances are found across intervention arms at baseline.

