## Results

The project was funded in September 2016, and enrollment began in May 2017. Enrollment will be completed between June and August 2019. Data analysis is currently underway, and the first results are expected to be submitted for publication in 2019.

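### Allocation ratios changed during recruitment, but Equation 1 has no randomization-period term, so the arm × TIME tests are open to confounding by enrolment cohort

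*Protocol article*

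**What the plan says.** Methods, Overview: "This study began recruitment in May 2017", and "From June 2018 to December 2018, the protocol underwent a process of review and revision". The revision had three major parts:

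- For STI tests, "to reduce STI testing frequency from every 4 months routinely to only at baseline, 12, and 24 months", with testing on request or for symptoms retained.
- Follow-up and intervention end at 12 months for youth who are neither MSM nor transgender.
- The third is "changing randomization allocations for person-mediated intervention arms to have statistical power for MSM and transgender participants with 70% retention rates".

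The Results section adds: "Enrollment will be completed between June and August 2019". Under Design, arm 1 has 690 participants, and arms 2 to 4 "have a sample size of 270 per arm with 220 MSM and transgender youth". Neither the old nor the new ratio appears, nor does the number enrolled under each.

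Outcome Measures makes repeat HIV and STI testing three times a year a component of the primary outcome.

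Data Analysis, Aim 1 prints Equation 1 with PEER, COACH, TIME, PEER × TIME, COACH × TIME, PEER × COACH × TIME and a random intercept. The interactions with TIME carry the primary goal. Equation 1 is called a starting point, and two elaborations are named. One is a choice of covariance structure by fit. The other is: "Covariates for demographics and other background characteristics may need to be added to Equation (1) if imbalances are found across intervention arms at baseline". The article nowhere says that the analysis accounts for the change in allocation.

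**The concern.** Within a period of constant allocation, the arms are comparable by design. When two periods with different ratios are pooled, each arm holds a different mix of early and late enrollees. If the two cohorts would have changed differently over follow-up without any intervention effect, that difference enters the arm × TIME coefficients. It can look like an intervention effect or hide one.

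The cohorts were also followed under different conditions, because the same revision reduced routine study-provided STI testing and testing is part of the primary outcome. The printed covariate rule does not protect against this. It names demographics and background characteristics, and it acts only after an imbalance is observed, so the data choose the model. A known change of design should be adjusted for regardless of what a baseline table shows.

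**Working it through.** **1. Timing.** From May 2017, the revision window (June to December 2018) is months 13 to 19 of a recruitment lasting 25 to 27 months (to June-August 2019). Both periods can therefore hold many participants.

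**2. How far the arm mixes can diverge.** Let N be the number enrolled before the change and a the fraction of them in arm 1. Both are assumptions. With the final sizes from Design:

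- early share of arm 1 = N·a / 690
- early share of arms 2-4 = N·(1 − a) / 810

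| N | a | Arm 1 | Arms 2-4 | Gap (points) |
|---|---|---|---|---|
| 750 | 0.50 | 375/690 = 54% | 375/810 = 46% | 8 |
| 1000 | 0.50 | 500/690 = 72% | 500/810 = 62% | 11 |
| 750 | 0.60 | 450/690 = 65% | 300/810 = 37% | 28 |
| 1000 | 0.60 | 600/690 = 87% | 400/810 = 49% | 38 |
| 900 | 0.60 | 540/690 = 78% | 360/810 = 44% | 34 |

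With wider assumptions (a from 25% to 60%, 40% to 70% enrolled early), the gap runs from −59 to +39 points. It is zero only if the early arm 1 share already equalled 690/1500 = 46%.

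**3. The plan's own power figure.** Sample Size Calculations states at least 80% power for 10 to 16 points at the last of 7 visits, with 160 per arm, random-intercept SD 1.5 and baseline rates of 20%, 50% and 80%. A logistic random-intercept simulation was run with 1000 datasets per scenario, a flat control arm and a Wald test of arm × TIME (two-sided 0.05 assumed, as the article gives no alpha). Reading the rates as population averages, power is 0.79 for +10 points at 80%, 0.87 for +16 at 50%, 0.88 for +16 at 20% and 0.89 for −16 at 80%. The stated figure is reproduced within about 1 point. Reading the rates as subject-specific does not reproduce it (0.58 for +16 at 50%).

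**4. Two-arm test with no true arm effect.** The same set-up was used, with the early cohort flat at 50% and the late cohort falling by 10, 20 or 30 points by month 24. Type I error without a period term:

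| Early share, arm 1 vs other arm | 10 points | 20 points | 30 points |
|---|---|---|---|
| 70% vs 51% | 0.056 | 0.099 | 0.187 |
| 78% vs 44% | 0.087 | 0.289 | 0.523 |
| 45% vs 75% | 0.080 | 0.201 | 0.452 |

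With period and period × TIME, all nine cells lie between 0.046 and 0.054. A rough guide to the bias is share gap × difference in change: 0.34 × 20 = 6.8 points in the middle cell of the second row.

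A level-only difference (40% in one cohort, 60% in the other, both flat) leaves the error at 0.05 to 0.06 without period terms, because the arm main effect absorbs it.

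**5. Equation 1 as printed, four arms.** This assumed 400 in arm 1, 160 in each other arm, 78% vs 44% early, and 400 datasets. A 20-point difference in change gives type I error of 0.42, 0.41 and 0.26 for PEER × TIME, COACH × TIME and PEER × COACH × TIME. With period terms the values are 0.04 to 0.06. A level-only difference gives 0.14 for the three-way term. That leak comes from the absence of a PEER × COACH term: adding it brings the value to 0.04.

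**6. Power and cost (two arms, 78% vs 44%, true 16-point effect at 50%).** With an opposing 20-point difference in change, power is 0.40 without period terms and 0.82 with them. With no period effect at all, adding the terms raises the standard error from 0.306 to 0.328 and lowers power from 0.865 to 0.823.

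**The case against.** **A steady secular trend is not enough.** A reader might infer that any calendar trend, such as rising PrEP use, biases the comparison. It does not. If the trend is linear on the logit scale, every cohort has the same slope and later entry shifts only the level, which step 4 shows to be harmless in a two-arm contrast. Bias requires different within-person change, through a nonlinear trend or the schedule change. This stands and limits the point.

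**The schedule change does not create a large gap at month 24.** A reader might infer that the testing indicator would show a very large spurious arm difference at the last visit. The first enrollee reaches month 24 in May 2019, after the revision process ended, so those visits fall under the new schedule for everyone. Testing on request or for symptoms continued, and no cut in HIV testing is listed. The cohorts differ mainly in year 1, which can tilt a fitted slope but does not support a claim about the final visit.

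**The shorter follow-up is not part of the problem.** The powered 24-month analysis is in MSM and transgender youth. Analyses that include cisgender-heterosexual youth are exploratory, at 12 months.

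**Size and direction are unknown.** This stands. The shares above also use all-youth arm sizes, whereas the arm 1 MSM/transgender number is not stated. With a 10-point difference in change the inflation is modest.

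**This may belong in the full plan.** Equation 1 is a starting point in a condensed article, and an external statistical expert took part in the revision. Period adjustment may therefore already be specified elsewhere. But the article does print a model and an adjustment rule, and that rule makes adjustment depend on observed imbalance. Followed as written, it leaves the arm × TIME tests unprotected.

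**Conclusion.** The point holds in limited form. The documents establish that allocation to arms 2-4 changed partway through recruitment, that routine STI testing was cut in the same revision, and that the printed model neither includes period nor has a rule that reliably would add it. The arm × TIME tests are valid only if early and late cohorts change alike over follow-up, and the schedule change makes that hard to take for granted.

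How much this matters cannot be read from the article. Under the assumed shares and differences in change, type I error ranges from barely above nominal (0.056) to more than half (0.523). These are conditional illustrations, not estimates for this trial. The direction could go either way.

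**What to change.** - Add randomization period (before or after the allocation change) and period × TIME to Equation 1 as fixed terms. Alternatively, estimate arm effects within each period and combine them. Do this whatever baseline imbalance is observed.
- State the date of the change, both ratios and the numbers randomized by arm and period, overall and for MSM and transgender youth.
- For the STI-testing indicator, also include which testing schedule was in force at each visit.
- Replace the imbalance-triggered rule with covariates fixed in advance, such as site.
- If the full analysis plan already does this, a sentence in the article saying so is enough.

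The change is to analysis wording and needs only each participant's randomization date, plus visit dates for the schedule term. The price is a slightly larger standard error, as in step 6 of the working. Because the Results section says that data analysis is already underway, the terms should be fixed before arm comparisons are seen.

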### Design

Figure 1 shows the study design overview. The randomized controlled factorial design assesses efficacy of 3 intervention strategies (arms 1-3) and their combination (arm 4). The person-mediated interventions in arms 2 to 4 have a sample size of 270 per arm with 220 MSM and transgender youth, whereas the larger sample of 690 in the automated intervention only (arm 1) is because of the broader U19 Cooperative Agreement’s goal to identify youth acquiring HIV infection during follow-up to refer to a sister protocol on acute HIV infection [45], and earlier expectations to recruit youth that could be referred to other ATN protocols. Participants are followed longitudinally over 24 months (12 months for youth who are not MSM or transgender) and assessed at 4-month intervals by interviewers. Participants also complete a brief 7-question survey every week by text message (or email when nonresponsive to text messages). The overviews of assessments are provided below and described in detail in linked publications for the U19 [17,44-47].

**Figure 1 figure1:**
[figure not shown]
Design of the randomized controlled trial for youth at high risk (YAHR) for acquiring HIV (n=1500). AMM: automated text-messaging and monitoring; MSM: men who have sex with men; SMS: short messaging service.

### Recruitment

In both Los Angeles and New Orleans, the Recruitment, Engagement, and Retention Centers in the Management Core [17] are responsible for recruiting, enrolling, and following up with youth. Youth are primarily recruited from CBOs and clinics serving gay, bisexual, and transgender youth; homeless youth; and youth on probation or released from incarceration. Youth are also recruited through dating apps (eg, Grindr, Jack’d, and Scruff), including while present in social venues (eg, bars, clubs, and community events). We anticipate the study sample to be predominantly MSM and transgender, African American and Latino, and aged between 18 and 24 years. Youth are approached with verbal assent to complete brief screener questions and a rapid HIV test; however, youth aged between 12 and 14 years are asked to provide written voluntary informed consent to screen because of IRB requirements. Details on recruitment and screening are provided in other publications from the U19 [17,47] and briefly summarized below.

### Eligibility

To screen as eligible for enrollment, youth must test seronegative on a rapid HIV testing at screening and report at least 3 of the following criteria: self-reporting as gay, bisexual, or transgender; African American or Latino race/ethnicity; having unprotected anal sex, sharing needles for injecting drugs, or an HIV-positive partner in the last 12 months; having been homeless (defined as not having a regular place to sleep for 3 or more months); illicit substance use (not including marijuana) in the last 12 months; having been hospitalized for a mental health disorder; having been in jail or on probation; having an STI in the last 12 months. Transgender and MSM youth are always eligible. Eligible participants are invited to enroll in the study with written informed consent.

### Assessments

Following enrollment, participants complete a baseline assessment, which includes a questionnaire and a series of rapid diagnostic tests. These assessments are repeated at follow-ups. Participants receive a US $50 cash incentive for each baseline and 4-month follow-up assessment completed. Other assessments include weekly monitoring surveys, staff implementation time and processes, and costing data for cost-effectiveness analyses. These assessments are briefly described below and in detail in Rotheram-Borus et al [17].

#### Rapid Diagnostic Tests

The following rapid diagnostic tests are performed (see Shannon et al for details [47]):

HIV—Rapid test: Clinical Laboratory Improvement Amendments (CLIA)-waived Alere Determine HIV-1/2 Ag/Ab Combo fingerstick blood test for HIV-1/2 antibodies and the HIV-1 p24 antigen with a detection window of 12 to 26 days; results are available in 20 to 30 min. Once enrolled, potential acute HIV infection is assessed in batches using the Cepheid Xpert HIV-1 Qual Assay to detect HIV-1 total nucleic acids for acute HIV infection, or lab-based polymerase chain reaction (PCR) testing.Chlamydia and gonorrhea—Food and Drug Administration–approved Cepheid Xpert CT/NG Assay PCR test using vaginal swabs from women, urine samples from men, and pharyngeal and rectal swabs from both women and men. Results are available in 90 min.Syphilis—CLIA-waived Syphilis Health Check fingerstick blood test to detect treponemal antibodies with a 10- to 15-min time to completion.Substance use—A multidrug urine test panel to detect the presence of marijuana, cocaine, opiates, and methamphetamine with result available in 2 to 5 min.Alcohol use—The BACtrack breathalyzer to determine blood alcohol content over the past 48 hours.

Any study participants who test positive for HIV are immediately linked to care for treatment and offered enrollment in one of the ATN Comprehensive Adolescent Research and Engagement Studies (CARES) protocols for youth living with HIV, depending on stage of HIV infection determined by Fiebig stages 1 to 6 on HIV-1 antibody using Western blot test [45]. Participants testing positive for other STIs are provided immediate treatment by the study team, including partner therapy.

### Questionnaires

Questionnaires are administered by an interviewer in a private room at partner sites or study offices, using Android tablets and take approximately 45 min to complete (see Rotheram-Borus et al for details [17]). Briefly, baseline questions cover lifetime and past 4 months; follow-up assessments cover the past 4 months. Questionnaires assess sociodemographic factors; health care access, insurance, and utilization; substance use; sexual behaviors; PrEP and PEP use; mental health; social media use; and locator information and consent to access medical records and to use social security numbers for locating efforts. Interviewers enter the participants’ responses and rapid diagnostic test results in the CommCare mobile-Web electronic assessment and case management system that is cloud based and Health Insurance Portability and Accountability Act (HIPAA) compliant, by Dimagi Inc (see Comulada et al for details [44]). CommCare also manages and sends intervention and assessment text messages as part of the automated text-messaging and monitoring intervention (AMM).

### Weekly Monitoring Surveys

The monitoring strategy is based on a weekly *Check-In* survey, which can be completed via text message or a Web link sent via email with a HIPAA–compliant RedCap version of the survey. Surveys assess the previous week time period with 7 questions on potential symptoms of acute HIV infection (yes/no), STI symptoms (yes/no), and number of days of feeling sad/depressed, sex without condoms, drug or alcohol use, not having a place to sleep or enough food; and miss taking medications (if taking medications). Participants receive a US $1 incentive per weekly survey completed, either in cash at their next 4-month follow-up assessment or on demand, including via electronic transfer (via Paypal, Venmo, or Zelle). Yes responses to HIV and STI symptom questions are reported to interviewers for follow-up risk assessment and rapid testing within 2 weeks. Reports on sadness/depression are monitored for potential follow-up and referral.

### Outcome Measures

Our primary outcome is uptake and adherence to the HIV prevention continuum, according to the following measures, which will be analyzed individually and in sum (see Statistical Methods below):

Linkage to medical care reflected in a visit twice annually, at a minimum, to a health care providerConsistent utilization of condoms, PrEP, or PEPParticipation in other HIV prevention programs and servicesRepeat assessments for HIV and STI testing 3 times annually

Secondary outcomes include mental health symptoms, substance use, and housing security, which are hypothesized to impact primary outcomes as mediators or moderators of intervention effects.

### Costing and Implementation Data

There are 2 types of costs: costs of delivering the intervention and the additional costs incurred by participants for their use of health care services and services from other agencies (eg, use of health care services). Intervention costs are classified into 1 of 4 categories [48]: (1) capital equipment (eg, computers); (2) recurring supplies and services; (3) facility space; and (4) personnel, including fringe benefits. Costs in the first 3 categories are obtained from project records. Personnel costs include hours and wages of staff to design and deliver the interventions, including peers, coaches, supervisors, facility charges, software costs, and short messaging service (SMS) and other social media costs, messaging and mobile app data costs, additional time in coaching and supervision, and server hosting. Personnel time is estimated from time reported on time sheets for hourly employees and budgeted time for other staff and investigators. Time spent on specific activities for hourly staff (eg, coaches and interviewers) is assessed in detail over 1-week periods quarterly using the Time It app [49] on their study-issued Android smartphones. Recorded time over 1-week periods is extrapolated to cover total time over the study period. The costs of additional services are derived from respondent reports on utilization and medical records and are estimated using publicly available data. Research-specific costs, such as incentive payments, informed consent, assessments, and software adaptation for survey tools, are excluded from total costs. All cost data are price-adjusted back to the first year of the study, using the medical care component of the consumer price index.

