###### Aim 3: To Assess the Relative Cost-Effectiveness of the Interventions

The deployment of all HIV prevention strategies today must be based on the cost-effectiveness of peer support and coaching to automated messaging for HIV prevention continuum outcomes and reducing risk behaviors, substance use, and mental health problems. The cost-effectiveness analysis will compare the additional cost required, on average, to get an additional unit of outcome in the 2 person-mediated interventions (peer support and coaching) and in the attentional control (automated messaging) by calculating a cost-effectiveness ratio (CER) [113]. The CER is the difference in total costs of providing a person-mediated intervention versus automated divided by the difference in person-mediated outcome and automated outcome [113]. Primary outcomes of HIV prevention continuum and secondarily substance use and mental health are outcomes of interest. Costs are measured as:

CER = (C_person_ − C_auto_) / (O_person_ − O_auto_). (3)

Analogous CERs will be calculated for peer support versus automated/attentional control, patient coaches versus automated, and for the combined peer support and coach versus automated control. CERs will be calculated at final the follow-up. We expect the person-mediated interventions to incur greater personnel costs than the automated ones. On the other hand, the person-mediated interventions may result in greater use of other mental health or drug treatment services than the automated group. These greater costs may or may not be offset by reduced costs of other services, such as incarceration, relative to the person-mediated groups. The CER answers the question of whether improvements in outcomes are worth any added costs. If the person-mediated interventions result in both better outcomes and lower net costs, it will be deemed *cost-saving*.

We conduct sensitivity analyses, as recommended by Gold [113] to estimate the extent to which the CER calculation is affected by differences in assumptions about the size of the differences in treatment effect. In particular, we determine how sensitive the CER is to assumptions that the difference in treatment effect is 1 SD below or above the mean estimated effect size. Similarly, we estimate the sensitivity of conclusions to costs that are 1 SD below or above the estimated mean.

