## Discussion

### Summary

The goal of this study is to test the efficacy and examine the cost-effectiveness and implementation of alternative models for delivering the CDC’s guidelines for routine HIV/STI testing for YAHR of acquiring HIV and for delivering evidence-based interventions in modular elements instead of scripted manuals and in flexible technology-based delivery formats. The technology-mediated interventions for YAHR in this study aim to improve HIV prevention continuum of engaging in medical care, adopting PEP after HIV exposure or PrEP before HIV exposure, or a behavioral protection strategy, as well as repeatedly testing for HIV and STIs. Consistent access and utilization of medical care is a common challenge for adolescents and young adults [114], particularly African American and Latino youth [115]. Text messaging and social media technologies offer relatively low-cost modalities to scale interventions for adolescents nationally. The study design provides opportunities to assess the efficacy, potential synergistic or cumulative effects, and cost-effectiveness of the proposed automated and person-mediated strategies. The study assessments will also enable examination of time trends in onset and periodicity of risk, and the relationships between primary and secondary outcomes in bivariate outcome analyses. In the evaluation of each intervention condition’s cost-effectiveness for the primary outcomes, we hypothesize that each intervention of increasing intensity (AMM, online peer support groups, and coaching) will have greater efficacy but that the added costs may not justify use at scale.

The mobile and social media intervention arms in this study build off the relatively nascent evidence base of internet, mobile, and social media interventions for populations at high-risk for acquiring or transmitting HIV [116-120]. Although technology-based assessments (eg, Web- and text-message surveys) [92,117] have demonstrated success with large samples in the thousands [121], mobile and social media technology intervention studies have tended to be in small scale by comparison [122]. Although several large-scale RCTs are currently underway to address HIV, most focus on a single technology-based strategy or a bundle of strategies in a single intervention arm, instead of a comparison of multiple strategies as in this study [120,123,124].

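### The cost-effectiveness ratios pool intervention design time with delivery cost at trial size, which does not fit the question of use at scale

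*Protocol article*

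**What the plan says.** Costing and Implementation Data names two types of cost: "costs of delivering the intervention and the additional costs incurred by participants". Within the first type, it states that "Personnel costs include hours and wages of staff to design and deliver the interventions, including peers, coaches, supervisors". The exclusions are confined to research items: "Research-specific costs, such as incentive payments, informed consent, assessments, and software adaptation for survey tools, are excluded from total costs". Intervention design is not among them. Time for staff who are not hourly comes from "budgeted time for other staff and investigators", and the article gives no split between design and delivery.

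Aim 3 defines the ratio on these totals: "The CER is the difference in total costs of providing a person-mediated intervention versus automated", divided by the difference in outcome. The only cost sensitivity analysis moves cost 1 SD below and above its estimated mean.

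The Discussion (Summary) says what the result is for. It hypothesises that interventions of increasing intensity "will have greater efficacy but that the added costs may not justify use at scale".

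**The concern.** Delivery cost grows roughly in proportion to the number of youth served. Design cost is mostly incurred before or early in delivery and does not. Once the two are pooled, the average cost per youth depends partly on how many youth the trial enrolled. According to the Design section, arm sizes were set by power among MSM and transgender youth and by the needs of sister protocols. Neither bears on the size of a future programme.

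The pooled figure is a fair answer to what the programme cost as run in the trial. It is a poor answer to whether the added cost is justified at scale. Moving cost by 1 SD neither separates design from delivery nor changes the number of youth over which design is spread. At stake is the interpretation of Aim 3. The efficacy analyses are unaffected.

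**Working it through.** The article states no design cost, delivery cost or CER, so there is no cost figure to reproduce. The arm sizes are consistent: 690 + 3 × 270 = 1500.

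**Inputs from the Protocol article**
- AMM alone: 690 youth; each person-mediated arm: 270 (Design).
- AMM goes to all arms, hence 1500 youth (Condition A/Arm 1).
- Peer support is used in arms 2 and 4, and coaching in arms 3 and 4 (Conditions B, C and D). Each component therefore serves 2 × 270 = 540 youth.
- Outcome difference dO, for illustration: 0.10 to 0.16 (Sample Size Calculations).

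**Assumptions, not in the documents**
- Design cost D per person-mediated component: $50,000 to $200,000.
- Roll-out size: 10,000 users.

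**Formulas.** Design adds D/n to the cost difference per youth, and D/(n × dO) to the CER. AMM design drops out of the difference if it is spread per head over all 1500 youth.

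| D (assumed) | n | D/n per youth | Added to CER at dO = 0.16 | Added to CER at dO = 0.10 |
|---|---|---|---|---|
| $50,000 | 540 | $93 | $579 | $926 |
| $200,000 | 540 | $370 | $2,315 | $3,704 |
| $50,000 | 10,000 | $5 | $31 | $50 |
| $200,000 | 10,000 | $20 | $125 | $200 |

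The CER columns are dollars per additional youth achieving the indicator. Arm 4 carries the design cost of both components: at $50,000 each, 100,000/540 = $185 per youth.

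**Does the direction hold?** Take $50,000 for AMM design and $50,000 for one component's design, with the component spread over 540 youth.
- AMM design per head over 1500: the increment is 50,000/540 = $93.
- AMM design charged to arm 1 only: 50,000/540 − 50,000/690 = 92.59 − 72.46 = $20.
- AMM design split equally over four arms: 92.59 + 12,500/270 − 12,500/690 = 92.59 + 46.30 − 18.12 = $121.

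Under the second rule the increment turns negative once AMM design divided by 690 exceeds component design divided by 540, that is, once AMM design is more than 690/540 = 1.28 times component design.

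**How large relative to delivery?** This too needs an assumption. With D = $50,000 and n = 540, design adds 92.59/300 = 31% to an assumed delivery cost of $300 per youth, but only 92.59/2,400 = 4% to one of $2,400.

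**The case against.** The strongest reply is that counting development cost is legitimate, and that a condensed article commonly leaves amortisation and the splitting of shared costs to the full plan. Both statements are true, and the absence of an amortisation rule is not the point here. The point is that the article's stated rule places design under a heading of delivery, feeds the total into the ratio, and uses that ratio for a question about scale.

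A reader might go further in four ways that the documents do not support.
- **That design cost falls on arms of 270.** Each component serves two arms, so 540 is the natural denominator. It may be larger still for coaching, since the article points to a sister protocol for details of that intervention.
- **That the rule certainly inflates the person-mediated CERs.** It does so if AMM design is spread per head over everyone who receives AMM, which is the natural reading. The article does not fix the allocation, however, and charging AMM design to arm 1 alone could shrink or reverse the effect.
- **That all design is one-off.** The Youth Advisory Boards section describes continuing improvement of the interventions, and forum content and coach training recur. Part of the work would recur at scale too.
- **That the rule favours a protocol hypothesis against the person-mediated arms.** The Discussion says only that added costs may not justify use at scale, and the abstract expects that online peer support may be more cost-effective.

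It is also fair to say that component-specific design may be modest. Coaching is not manualised, the forum runs on an existing platform, and the most fully described development work, adapting the text-message libraries, belongs to AMM. The size is therefore open. A small effect would still not make the pooled ratio the right one for scale.

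**Conclusion.** The concern holds as a mismatch between the stated costing rule and the stated use of the result. Design time is expressly included, is not on the exclusion list, enters the CER through total costs, and is not isolated by the planned sensitivity analysis. The ratio then depends in part on trial size, which does not suit a question about scale.

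The size is unknown. The figure of $93 to $370 per youth rests on the assumed design cost, the denominator of 540 and per-head allocation of AMM design; the comparison of $5 to $20 also rests on the assumed 10,000 users. The upward direction depends on the allocation as well. Including design cost is not an error for the programme as run in the trial. What is unsupported is carrying that one figure over to use at scale.

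**What to change.** In **Costing and Implementation Data**, separate design and start-up cost from delivery cost:
- by date for time before enrolment began in May 2017;
- by activity code afterwards;
- with an estimated split for staff entered at budgeted time.

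State that shared design cost is allocated per head across the arms that use the component: AMM over 1500 youth, and peer support and coaching over 540 each.

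In **Aim 3**, report each CER with and without design cost. Base statements about use at scale either on delivery cost, or on delivery cost plus design cost spread over a stated roll-out size. Delivery cost need not become the only base case.

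The work is small: an extra cost code and an extra line of results. The downsides are that a second ratio is reported and that the split of past budgeted time will be approximate. Hourly staff activity is recorded only in sampled weeks, so its split will also carry some error.
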